## Abstract

**Introduction:**

Emotional problems are leading contributors to health burden among adolescents worldwide. There is an urgent need for evidence-based psychological interventions for young people. This study aims to evaluate the effectiveness of a school-based, group psychological intervention, Early Adolescent Skills for Emotions (EASE) developed by the WHO to improve psychosocial distress in Pakistani adolescents.

**Method and analysis:**

A two-arm, single-blinded, cluster randomised controlled trial, with a wait-list control arm is being conducted in school settings of rural Pakistan. Forty eligible public-school clusters have been randomised (stratified by gender) on a 1:1 allocation ratio into intervention (n=20) and control arm (n=20). Following informed consent, 564 adolescents with psychosocial distress (Youth-reported Paediatric Symptoms Checklist, cut-off ≥28) from 40 schools have been enrolled into the trial (14±3 average cluster size) between 2 November 2021 and 30th November 2021. Participants in the intervention arm will receive EASE in 7-weekly adolescents and 3-biweekly caregivers group sessions in schools. The adolescent sessions involve the components of psychoeducation, stress management, behavioural activation, problem-solving and relapse prevention. Caregivers will receive training to learn and implement active listening; spending quality time and using praise as a strategy to help their children. The primary outcome is reduction in psychosocial distress at 3 months postintervention. Secondary outcomes include symptoms of depression and anxiety, caregiver–adolescent relationship and caregivers’ well-being. Outcomes will be assessed at baseline, immediate 1 week and 3-months postintervention. Qualitative process evaluation will explore barriers and facilitators to programme implementation in low-resource school settings.

**Ethics:**

Ethics approval has been obtained from Central Ethics Committee of University of Liverpool, UK, Ethics Review Committee of WHO Geneva and from the Institutional Review Board of Human Development Research Foundation (HDRF), Pakistan.

**Dissemination:**

The findings of the study will be disseminated by WHO and through peer-reviewed publications.

**Trial registration number:**

ISRCTN17755448.

STRENGTHS AND LIMITATIONS OF THIS STUDYTo help young adolescents with internalising problems, a transdiagnostic psychological intervention was developed by WHO called ‘Early Adolescent Skills for Emotions (EASE)’. The intervention is designed to be delivered through non-specialist facilitators in low-resource settings.A two-arm, single-blinded, cluster randomised controlled trial, with a wait-list control arm, adequate sample size and power and an embedded qualitative process evaluation is being conducted to evaluate the effectiveness and cost-effectiveness of EASE in school settings of Pakistan.The study is being conducted in one rural geographical area of Pakistan and may need more studies in other areas for generalisability.The study uses self-reported measures for most outcomes. However, these are considered standard and used widely in the field.

## Introduction

Schools are an important public health platform to promote positive youth mental health globally.^1 2^ Schools are uniquely placed to reach significant numbers of young people to address their mental health needs, especially in low-income and middle-income countries (LMICs), where a lack of child and adolescent mental health services and experts; lack of access to mental health services; low awareness of mental health, and economic and societal barriers such as stigma remain key challenges to the provision of evidence-based mental health services.^3^ There is growing evidence from both high income and LMICs that school-based mental health programmes are associated with beneficial mental health outcomes in adolescents.^1 2^ However, scale-up and sustainable implementation of mental health programmes for young people in LMICs demands political will, stakeholder involvement, intersectoral coordination and leadership often between health and education sectors,^4^ particularly in a post-COVID context, where 91% of the world’s student population has been negatively impacted by closures of schools due to COVID-19 pandemic.^5^

Rates of anxiety and depression in young people have been exacerbated during COVID-19 pandemic.^6^ Moreover, due to exacerbation of psychosocial stressors including alteration in daily routine and social interactions during COVID-19 pandemic, at-risk adolescents are more likely to develop severe psychological problems. This situation demands an urgent need to provide more effective mental health support to school going adolescents to ensure that young people with symptoms of distress have access to the support that they need in their schools.

Youth in Pakistan account for 35% of its population (below the age of 14 years) and are exposed to a number of chronic adversities such as poverty, violence and socio and economic inequalities which makes them more susceptible to develop mental health problems early in their adolescence.^7^ In addition, the ongoing COVID-19 pandemic situation is adversely affecting the economic, social and emotional well-being of the population at large and is particularly negatively impacting the well-being of adolescents due to nationwide lockdowns, closure of schools and disruption of academic year.^8^ A recent epidemiological study, conducted pre-COVID-19, with 5856 adolescents from 41 public schools in rural Pakistan reported 25% prevalence rate of psychosocial distress in school going adolescents.^9^

Recognising the ever-growing burden of adolescent mental health problems in Pakistan, the Ministry of Health in Pakistan has launched the President’s programme to promote youth mental health through schools.^10^ It emphasises the role of early-life interventions to promote mental health and prevent mental illnesses and takes a multitiered approach and recommends training non-specialists such as ‘university graduates’ to promote socioemotional well-being of school-going adolescents. Under the ambit of President’ Programme, Early Adolescents Skills for Emotions (EASE), is being implemented in public schools of rural Pakistan to address internalising problems in school-going adolescents. EASE was developed by WHO as a brief, transdiagnostic group psychological intervention designed to be delivered by non-specialists, to help young people aged approximately 10 to 14 years experiencing internalising problems such as psychosocial distress and symptoms of depression and anxiety^11^ (for more details on intervention please see section on interventions below). EASE has been previously translated in Urdu (National Language of Pakistan), culturally adapted for implementation in public schools and feasibility tested in eight public schools of rural Pakistan using a feasibility cluster randomised controlled trial (cRCT) design (trial registration NCT04254393). The results of the evaluation demonstrated the acceptability and feasibility of the adapted intervention to be delivered by non-specialist facilitators in public school settings of Pakistan and exhibited promising effects on improving adolescent’s well-being.^12^

This study aims to evaluate the effectiveness and cost-effectiveness of the culturally adapted EASE intervention compared with wait-list control to improve psychosocial distress in adolescents and improve caregiver-adolescent relationship and caregivers’ well-being at 3 months postintervention in public school settings of Pakistan.

### Hypotheses

Our primary hypothesis is that *EASE* will be superior compared with *waitlist control*, in reducing the psychosocial distress in adolescents (aged 13–15 years), measured with the self-rated Paediatric Symptom Checklist (PSC) at 3 months’ postintervention. Our secondary hypotheses are that *EASE* will result in improving adolescent well-being, quality of life, problem-solving skills, perceived emotional support, caregiver–adolescents relationship and caregivers’ well-being and reducing somatic complaints and anxiety and depressive symptoms in adolescents.

## Methods and analysis

### Study design

A two-arm, single-blind, cRCT, with a wait-list control arm and an embedded qualitative study is being conducted in public schools of rural subdistrict of Gujar Khan in Rawalpindi, Pakistan. The unit of randomisation is a school. In this study, 40 eligible school clusters, stratified by gender, have been randomised into intervention and control arms with a 1:1 allocation ratio. Outcomes will be assessed at baseline and 1 week and 3 months postintervention.

### Patient and public involvement

The research team has culturally adapted and feasibility tested the intervention by working collaboratively with the adolescents, caregivers and school administration from the same study subdistrict. As a part of the formative phase we conducted (1) qualitative needs assessments with school adolescents to identify the priority adolescent mental health problems; (2) end-user testing workshops with adolescents in school settings to culturally adapt the EASE intervention and (3) consultative workshops with relevant stakeholders from Ministries of education and health of Pakistan, school staff including head teachers, teachers and mental health experts, parents and adolescents to develop a hypothesised pathway for the implementation of school based mental health programmes in low resource settings of Pakistan.^13^ Once the current trial is complete, the findings will be disseminated to participants, ministries of health and education, school education department and wider public through presentations at community and public forums.

### Study settings

The study will be conducted in 40 middle and high public schools of rural subdistrict of Gujar Khan, located in the Rawalpindi district in the province of Punjab in Pakistan (approx. population of 1000 000). It is a pilot site for the implementation of President’s Mental Health Programme and falls under the catchment area of Institute of Psychiatry (IoP), Benazir Bhutto Hospital, Rawalpindi which is the sponsoring institute of this study. The subdistrict is semirural, with agrarian-based economy and represents typical rural area in the country. The population speaks Punjabi with Potohari being the predominant dialect. In Gujar Khan subdistrict, there are 497 public schools (323-primary, 89 middle and 85 high schools). There are 231 schools for boys and 266 schools for girls in Gujar Khan in total. The primary decision body for public schools in Gujar Khan is District Education Department and with its permission 40 public schools (20 boys and 20 girls schools) were included in this study. Literacy rates in the study district are 80%.^14^

Mental health services in Pakistan are provided through specialist mental health units at tertiary healthcare facilities, concentred in urban centres with little or no mental healthcare for rural populations. School health services in public schools are provided through School Health and Nutrition Supervisors, who are based at primary healthcare (PHC) centres and visit schools once a month to screen students for Eye, ears, nose and throat, dental, skin and general physical problems and if any health problems are identified, the students are referred to the medical officer of the concerned PHC centres.

### Research participants

The age range of adolescents in school studying in academic grades 8–10 are 13–15 years of age. Our formative work indicated that challenges faced by adolescents in grades 8–10 include academic stress, expectations of high academic achievements from parents and teachers, peer pressure, interpersonal problems, worries about the future and stressful home environment (publication forthcoming). These stressors often lead to mental health problems including distress, anxiety and depression like symptoms among adolescents. The need for focused psychological support for the mental health of adolescents in this age group has been identified as a priority by the education sector stakeholders.

The research participants for the current study are adolescents, screened positive for psychosocial distress with cut-off score of ≥28 on self-rated PSC (validated cut-off score for school going adolescents in Pakistan).^9^

### Eligibility criteria of participants

#### Inclusion criteria

Adolescents aged 13–15 years.Living with parents/primary caregivers, attending public middle and high schools in the Gujar Khan sub-district of Rawalpindi, Pakistan.Written parent/primary caregiver informed consent or witnessed consent and adolescent assent for participation in the study.Screened positive on self-reported PSC (cut- off score ≥28).Where there is more than one eligible child in a family unit, we will include the youngest eligible child.

#### Exclusion criteria

Adolescents at high risk of imminent suicide as reported by the students themselves, or parents/primary caregivers, or identified by the trained assessment team (AT) during screening.Adolescents with acute medical conditions who require immediate or ongoing in-patient medical or psychiatric care, as reported by student themselves or parents/primary caregivers or identified by the trained AT during screening.Adolescents with deafness, blindness and speech difficulties or with a severe mental, neurological or substance use disorders (eg, psychosis, mutism, intellectual disability, autism or drug dependence) identified by the trained AT during screening.

### Sample size calculations

The cluster unit of randomisation has been defined at the school level, stratified by gender. Based on other school-based and community-based mental health interventions using the measures assessing psychosocial problems in children,^15 16^ we assume an effect size of 0.4 at 3 months’ postintervention follow-up, with 80% power, 0.05 significance, an ICC of 0.05 and a two-sided hypothesis test with 40 school clusters randomised with a 1:1 allocation ratio, stratified by gender and accounting for 20% attrition. This results in a total of 550 adolescents (ie, 225 in each arm) and about 14 adolescents from each school. Each high school has about 150 adolescents in grade 8 and 9, which is more than sufficient to meet our sample size requirement. Stratification by gender will minimise imbalance between groups by factors likely to be associated with our outcome and reduce the between-cluster variability, hence increasing the power of the study.

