### Randomisation and blinding

The unit of randomisation is schools, which will be stratified by gender. Forty middle and high schools nominated by district education authority have been enrolled in the cRCT. Schools will be randomised on 1:1 allocation ratio by independent researcher using computerised software. The 40 schools will be randomised into intervention (n=20) and control arm (n=20). A total of 550 adolescents with psychosocial distress will be recruited from all randomised schools (10–14 adolescents from each cluster). Allocation concealment will be ensured by keeping the random assignments in sequentially numbered sealed envelopes. Due to the nature of the intervention, it is not possible to blind parents, adolescents, school counsellors, intervention supervisors, data and trial manager to the treatment allocation status of trial participants. The AT and principal investigators (PIs) will be blind to the allocation status of school clusters, while the qualitative research team will be un-blind to allocation status of school clusters. To maintain blinding during the trial, intervention and AT will not have any interaction during the trial by being based at separate office locations. The AT will also be non-residents of study subdistrict, Gujar Khan. Furthermore, participants including parents, school administration, head teachers and adolescents will each be individually instructed not to disclose to the AT which type of training they are receiving prior to the commencement of any assessment. Fidelity of blinding will be measured by having assessors guess the condition of each participant at the end of each assessment. We hypothesise that assessors will only be able to correctly guess the condition of participants at a chance rate of nearly 50% at follow-up assessments, indicating that blinding is maintained. The trial statistician will also be blind to the allocation status when developing the statistical analysis plan and writing the statistical programmes. The statistical analysis plan will be validated using dummy randomisation codes. The allocation status of research participants will only be disclosed in a trial steering committee (TSC) meeting after locking of the database on the completion of the trial. In the event of un-blinding, the point of unblinding will be recorded, the assessment will be halted and another assessor will be assigned to complete assessments for that cluster.

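### The sample-size statement equates 550 in total with 225 per arm, and neither figure follows from the stated 80% power, effect 0.4 and ICC 0.05

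*Protocol article*

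**What the plan says.** The Sample size calculations section of the protocol article gives every input. On the effect: "we assume an effect size of 0.4", at the 3-month follow-up. On the test and clustering: "with 80% power, 0.05 significance, an ICC of 0.05 and a two-sided hypothesis test with 40 school clusters", with 1:1 allocation, stratified by gender and "accounting for 20% attrition". The result is: "This results in a total of 550 adolescents (ie, 225 in each arm) and about 14 adolescents from each school".

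The Randomisation and blinding section repeats 550 as the recruitment target and adds a range, "10–14 adolescents from each cluster". The abstract reports 564 adolescents enrolled from the 40 schools, with an average cluster size of 14±3.

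**The concern.** There are two separate faults in one sentence.

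- The total and the per-arm number cannot both be right under equal allocation: they differ by 100 adolescents. The sentence offers 225 as a restatement of 550, not as a number left after attrition.
- The inputs are complete enough to rerun the calculation, and they lead to neither 550 nor 450. At least one printed input or result is therefore not the one that was used.

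The planned size, power and ICC are what the trial report will carry forward and what readers will use to judge how informative the result is. The box on strengths and limitations also calls the sample size and power adequate, and this calculation is the only support the article gives for that.

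**Working it through.** **Inputs, all from Sample size calculations:** effect 0.4 (no SD is given, so it is taken as a standardised difference with SD 1); two-sided alpha 0.05; power 80%; ICC 0.05; 40 schools, 20 per arm; attrition 20%; about 14 per school.

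**1. The printed counts against each other**
- 550 / 40 = 13.75 per school, which agrees with about 14.
- 550 / 2 = 275 per arm.
- 2 × 225 = 450, or 11.25 per school, which agrees with neither.
- Attrition does not close the gap: 550 × 0.8 = 440 (220 per arm, not 225); 450 / 0.8 = 562.5; 450 × 1.2 = 540.

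**2. Required number at the stated inputs**
- Individually randomised: n = 2(1.96 + 0.8416)² / 0.4² = 98.1 per arm.
- Design effect: DE = 1 + (m − 1) × ICC.
- m = 14 recruited: DE = 1 + 13 × 0.05 = 1.65; 98.1 × 1.65 = 161.9 evaluable per arm; / 0.8 = 202.4 per arm; about **405** in total.
- m = 11 analysed (13.75 × 0.8): DE = 1.50; 98.1 × 1.50 / 0.8 × 2 = about **368** in total.
- Fixing 20 schools per arm and solving 20m / (1 + 0.05(m − 1)) = 98.1 gives m = 6.2, so 247 evaluable and about 309 recruited. A t-test with 38 df raises this to about 331.

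The largest of these is 405. The printed 550 is 36% above it (550 / 405 = 1.36), and 450 is 11% above it (450 / 405 = 1.11).

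**3. Power that the printed numbers give, after 20% loss**

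Effective n per arm = 20m / DE; SE = √(2 / effective n).

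| Recruited | Analysed per school | DE | Effective n per arm | Power, t (38 df) | Power, normal |
|---|---|---|---|---|---|
| 550 | 11 | 1.50 | 146.7 | 91.6% | 92.9% |
| 450 | 9 | 1.40 | 128.6 | 87.8% | 89.4% |

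If the 14±3 in the abstract is read as a mean and SD, the coefficient of variation of cluster size is 3/14. That lowers the normal figure for 550 only to 92.5%.

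**4. Effect detectable at 80% power with 550 recruited**
- SE = √(2 / 146.7) = 0.117.
- Normal: 2.80 × 0.117 = 0.33. With t on 38 df it is about 0.34.

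**5. Can the inputs that were used be recovered?** Several sets land near the printed numbers:
- 90% power, ICC 0.05, m = 14: 131.3 × 1.65 / 0.8 × 2 = 542 in total.
- 90% power, ICC 0.07, m = 11: 131.3 × 1.70 = 223 evaluable per arm; / 0.8 × 2 = 558 in total.
- 80% power, ICC 0.10, m = 14: 98.1 × 2.30 = 225.7 evaluable per arm; / 0.8 = 282 per arm; 564 in total.

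None of them is singled out by the text.

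**The case against.** The best defence is that 225 is a one-digit slip for 275. Every other count is coherent: 550 agrees with about 14 per school, with the target repeated under Randomisation and blinding, and closely with the 564 enrolled. The remaining discrepancy runs in the safe direction, recruitment is complete, and neither the analysis nor the enrolment would change. All of this stands, and it limits the seriousness of the point. It does not explain why 80% power is printed beside a number that gives about 92%.

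Three stronger readings are tempting, and the documents do not support them:

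- **The design ICC was really 0.10.** A reader might infer this because it yields both about 225 evaluable per arm and 564 in total. But other input sets come about as close. Moreover, 564 is the number enrolled, whereas the planned number is 550 in both places. By the method in step 3, 282 enrolled per arm at ICC 0.10 would also give 83–85% power rather than 80%.
- **The range of 10 to 14 per school contradicts 550.** It implies 400 to 560 over 40 schools. However, 13.75 lies inside the range, and schools differ in size. This is loose but not an error.
- **The trial is underpowered, or its claim of adequate power fails.** At the stated inputs the opposite holds.

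**Conclusion.** Wrong as written; a moderate reporting correction. Under 1:1 allocation, 550 in total and 225 per arm are incompatible by 100 adolescents, and 225 is the figure out of line with the rest. Neither total reproduces from the stated inputs, which need about 405 recruited (about 368 with the design effect at 11 analysed per school). With 550 recruited and 20% lost, power is about 92–93% rather than 80%.

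This rests on 0.4 being a standardised difference and on no variance reduction from baseline adjustment or stratification; either would lower the required number further and widen the gap. Which input was misreported cannot be told from the article, so no particular alternative ICC or power should be asserted as the true design value.

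**What to change.** In Sample size calculations:

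1. Replace 225 per arm with 275. If 225 was meant as the evaluable number, label it so and reconcile it with 550 × 0.8 = 440, which is 220 per arm.
2. Restate the calculation with the effect size, power, ICC, cluster size and attrition actually used when the trial was designed, taken from the sponsor's design records and not chosen now to fit the enrolled number. Say whether the design effect uses recruited or analysed cluster size.
3. If ICC 0.05 and effect 0.4 were the design values, state about 92% power for 550 recruited with 20% loss, or equivalently a detectable effect of about 0.33–0.34 at 80% power.

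The cost is wording only. No participants are added and the analysis does not change. It should be done before the trial report quotes the planned sample size.
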